## Abstract

**Background:**

Ventilator-associated tracheobronchitis is a common condition among invasively ventilated patients in intensive care units, for which the best treatment strategy is currently unknown. We designed the VATICAN (Ventilator-Associated Tracheobronchitis Initiative to Conduct Antibiotic Evaluation) trial to assess whether a watchful waiting antibiotic treatment strategy is noninferior to routine antibiotic treatment for ventilator-associated tracheobronchitis regarding days free of mechanical ventilation.

**Methods:**

VATICAN is a randomized, controlled, open-label, multicenter noninferiority trial. Patients with suspected ventilator-associated tracheobronchitis without evidence of ventilator-associated pneumonia or hemodynamic instability due to probable infection will be assigned to either a watchful waiting strategy, without antimicrobial administration for ventilator-associated tracheobronchitis and prescription of antimicrobials only in cases of ventilator-associated pneumonia, sepsis or septic shock, or another infectious diagnosis, or to a routine antimicrobial treatment strategy for seven days. The primary outcome will be mechanical ventilation-free days at 28 days, and a key secondary outcome will be ventilator-associated pneumonia-free survival. Through an intention-to-treat framework with a per-protocol sensitivity analysis, the primary outcome analysis will address noninferiority with a 20% margin, which translates to a 1.5 difference in ventilator-free days. Other analyses will follow a superiority analysis framework.

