### Sample size

The sample size calculation was based on the demonstration of noninferiority of the watchful waiting strategy compared to the use of antibiotics for 7 days strategy. A sample size of 295 patients per group (total of 590 patients), with a one-sided t test for noninferiority (with a significance level of 0.05), has 80% power to reject the null hypothesis that the number of VFDs at 28 days in the Watchful Waiting Group is inferior to the number of VFDs at 28 days in the Antibiotic Treatment Group for 7 days by a margin of 20% and a coefficient of variation of 1.38,^(7)^ considering a potential loss to follow-up or dropouts of 10%.

The choice of the 20% noninferiority margin was motivated by what was considered acceptable by the Steering Committee from a clinical perspective. This 20% noninferiority margin translates into a 1.5 VFD difference at 28 days, considering the mean VFD of 7.69 days and the standard deviation (10.67) in patients with VAT from a prior publication.^(7)^

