### Statistical analysis

The main analysis will follow the intent-to-treat framework, where the null hypothesis is that the number of VFDs up to 28 days in the Watchful Waiting Group is less than the number of VFDs in the Antibiotic Treatment Group for 7 days by a margin of 20%. If the upper bound of the 95% confidence interval for inferiority of the Watchful Waiting Group is < 20%, we will reject the null hypothesis of inferiority. To estimate the effect of treatment on the primary outcome, as well as in the interim analyses, an appropriate statistical model adjusted for stratification variables will be used for this type of outcome according to the variable behavior: either a generalized additive model for location scale and shape with zero-inflated beta distribution or nonparametric tests with the calculation of measures of effect and confidence intervals using resampling techniques (bootstrap) can be used. The effect size will be estimated according to the model best fitted to the data, with a 1-sided 95% confidence interval (95%CI) for noninferiority. If the noninferiority hypothesis is satisfied, superiority for the primary outcome will be tested considering a 95%CI using a hierarchical closed testing procedure. A primary sensitivity analysis of this noninferiority analysis will be a per-protocol analysis. Although per-protocol analyses are usually the primary analysis framework recommended for noninferiority trials, the intention-to-treat analysis framework may lead to more conservative estimates in antimicrobial trials.^(29)^ A p value of 0.05 will be considered to indicate statistical significance in the final analysis.

We also performed preplanned sensitivity analyses of the primary outcome, including only patients with microbiologically confirmed VAT, and we analyzed the randomization groups as an instrumental variable. Preplanned subgroup analyses will include the following: patients with or without a diagnosis of coronavirus disease 2019 (COVID-19) or other viral pneumonia, age ≤ 60 or > 60 years old, diagnosis of trauma on admission, acute brain injury, invasive mechanical ventilation duration of ≤ 5 or > 5 days at the time of randomization and effective vs. ineffective empirical antimicrobial treatment for isolated pathogens.

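### The 20% noninferiority margin is not tied to a scale: it equals 1.5 VFDs only near a control mean of 7.5 to 7.7, and the decision rule does not say 20% of what

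*Protocol article*

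**What the plan says.** The protocol article states the margin in three places.

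- **Abstract, Methods.** Both forms appear, with no condition attached: "noninferiority with a 20% margin, which translates to a 1.5 difference in ventilator-free days".
- **Sample size.** The calculation is described as "by a margin of 20% and a coefficient of variation of 1.38", with one-sided alpha 0.05, 80% power and 10% loss, giving 295 per group. The next paragraph supplies the conversion and its condition: "This 20% noninferiority margin translates into a 1.5 VFD difference at 28 days, considering the mean VFD of 7.69 days", with a standard deviation of 10.67, both from an earlier publication on patients with VAT.
- **Statistical analysis.** The operative rule is on the percentage alone: "If the upper bound of the 95% confidence interval for inferiority of the Watchful Waiting Group is < 20" per cent, inferiority is rejected. No denominator is given. The model is left open between a zero-inflated beta GAMLSS and nonparametric tests with bootstrap intervals, and the effect size is to come from whichever fits best.

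**The concern.** A noninferiority margin has to be one number on one scale, because the primary claim is a comparison of an interval bound with that number. Here the percentage and the number of days are linked only through a planning mean. If the trial's antibiotic arm has a different mean, they separate.

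The rule could then be read in at least three ways: a ratio of mean VFDs with both means estimated, a loss expressed as a percentage of the observed control mean, or a fixed loss of about 1.5 VFDs taken from the historical mean. Because the model is chosen by fit, the scale of the effect estimate does not settle the question either. The noninferiority conclusion, the type I error at a given true loss, and the power all depend on which reading is used.

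**Working it through.** **Inputs.** From Sample size: mean 7.69, SD 10.67, CV 1.38, margin 20%, one-sided alpha 0.05 (z = 1.645), power 80% (z = 0.842), loss 10%, 295 per group. Evaluable per group: 295 × 0.9 = 265.5, so 265 or 266. The control means, observed effects and the SD of 10 in steps 3 and 4 are assumptions for illustration and are not in the document.

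**1. The plan's own figure.**
- Log-ratio form: SD on the log scale = √ln(1 + 1.38²) = 1.0326; margin = −ln 0.80 = 0.2231. n = 2 × (1.645 + 0.842)² × 1.0326² / 0.2231² = 265 per group; 265 / 0.9 rounds up to 295. This matches.
- Difference form, margin 1.538, SD 10.67: 596 evaluable, 663 with loss. No match.
- Difference form, margin 1.5: 626 evaluable, 696 with loss. No match.
- Difference in units of the mean, margin 0.2 and SD 1.38: 589 evaluable, 655 with loss. No match.
- Untransformed ratio, variance factor 1 + 0.8² = 1.64: 1.38² × 1.64 × (2.487 / 0.2)² = 483 evaluable, 537 with loss. No match.

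Of the forms tried, only the log-ratio margin of 0.80 gives 295.

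**2. Where the two forms agree.** 0.20 × 7.69 = 1.538, and 1.5 / 7.69 = 19.5%. Exact equality needs a mean of 1.5 / 0.20 = 7.50. At 7.69 the gap is 0.04 day.

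| Control mean | 20% in VFDs | 1.5 VFDs as % |
|---|---|---|
| 5 | 1.0 | 30% |
| 6 | 1.2 | 25% |
| 7.5 | 1.5 | 20% |
| 10 | 2.0 | 15% |
| 12 | 2.4 | 12.5% |

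**3. Same data, different verdicts.**
- *Control mean 12, loss 0.6, SD 10.67, 265 per group.* SE = 10.67 × √(2/265) = 0.927; upper bound for the loss = 0.6 + 1.645 × 0.927 = 2.12 VFDs. This is below 2.4 and above 1.5. With both means estimated: 11.4 − 0.8 × 12 = 1.8; SE = 10.67 × √(1.64/265) = 0.84; lower bound = 1.8 − 1.645 × 0.84 = +0.42. The relative rule passes either way; 1.5 fails.
- *Control mean 5, watchful waiting better by 0.3, SD 10.67, 266 per group.* SE = 0.925; bound = −0.3 + 1.645 × 0.925 = 1.22 VFDs, or 24.4%. Estimated contrast: 5.3 − 4.0 = 1.3; SE = 10.67 × √(1.64/266) = 0.838; lower bound = 1.3 − 1.378 = −0.08. Here 1.5 passes and 20% fails.
- *Two readings of 20% itself: control mean 6, watchful waiting better by 0.2, SD 10, 266 per group.* Control mean treated as fixed: bound = −0.2 + 1.645 × 10 × √(2/266) = 1.23 VFDs = 20.4%, a fail. Both means estimated: 6.2 − 4.8 = 1.4; SE = 10 × √(1.64/266) = 0.785; lower bound = 1.4 − 1.292 = +0.11, a pass.

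**4. Error rate.** Control mean 10, true loss 1.5 VFDs, SE 0.925, control mean treated as fixed: the 20% rule (2.0 VFDs) passes with probability Φ((2.0 − 1.5)/0.925 − 1.645) = 13.5%, against 5% if 1.5 were the margin.

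**5. Power by scale, no true difference, 266 evaluable, planning mean and SD.**
- Difference of 1.5: Φ(1.5/0.925 − 1.645) = 49%.
- Difference of 1.538: 51%.
- Contrast mean(watchful waiting) − 0.8 × mean(antibiotic): Φ(1.538/0.838 − 1.645) = 58%.

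**The case against.** The strongest reply is that there is only one rule. Statistical analysis states both the null hypothesis and the rejection criterion as 20%. The 1.5 figure is introduced as a conversion, with its planning mean beside it in Sample size. A reader might infer that the protocol holds two competing decision thresholds that contradict each other. It does not: 1.5 never appears in a rejection rule, and this part of the reply stands in full.

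It also stands that the sample size inputs, a percentage margin with a coefficient of variation, point to a relative scale.

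A reader might further infer that the sample size is wrong. The document does not support that, because 295 is reproduced exactly on the log-ratio scale. The lower powers apply only if another scale is adopted.

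Nor does the document show that the control mean will differ from 7.69. The trial's exclusions make a shift plausible, but the selection of the source cohort is not visible.

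Finally, details of the primary model are deferred to an analysis plan due before database closure, and the trial statisticians are blinded. This lowers the risk of a choice made with results in view. It does not remove the point: the margin and the rule are already written here, and they are written so that 20% has more than one meaning.

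**Conclusion.** The point holds as an ambiguity in the primary decision threshold, not as a contradiction between two rules. The article fixes the percentage but not its denominator or scale, and the Abstract presents 1.5 VFDs as an unconditional equivalent, which it is only near a control mean of 7.5 to 7.7.

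If the control mean departs from that range, verdicts can differ in either direction. Even the readings of 20% can disagree, according to whether the control mean is treated as known. How often this would happen cannot be said from the document, because the examples rest on assumed means and effects.

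The power consequence is firmer, since it uses the article's own planning values: the stated 80% goes with a log-ratio calculation, against about 49% for a 1.5-day difference and about 58% for the untransformed 0.8 contrast.

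**What to change.** Before any unblinded comparison, name one binding margin and write the inequality on its scale. The relative margin is what Statistical analysis and the sample size inputs point to: noninferiority is concluded if the lower one-sided 95% bound for the ratio of mean VFDs, watchful waiting to antibiotic, exceeds 0.80, with both means estimated. In the Abstract and Sample size, label 1.5 VFDs as illustrative at the assumed mean of 7.69. Whichever model is fitted, require it to deliver the effect on the named scale.

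State the power for that scale and analysis. Naming the ratio does not by itself secure 80%. Tested on untransformed days, it is the 0.8 contrast, with about 58% power under the planning values. The log-ratio calculation assumes a lognormal outcome, whereas nonsurvivors are assigned zero VFDs, which have no logarithm.

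The edit is to wording in the protocol and analysis plan. The real cost is that the stated power becomes less favourable if the difference or the untransformed contrast is chosen. Timing matters: the first interim look is planned at 196 patients, and the article already reports more than 180 included.

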**Conclusion:**

The VATICAN trial will follow all national and international ethical standards. We aim to publish the trial in a high-visibility general journal and present it at critical care and infectious disease conferences for dissemination. These results will likely be immediately applicable to the bedside upon trial completion and will provide information with a low risk of bias for guideline development.

## INTRODUCTION

The use of invasive mechanical ventilation (IMV) for organ support is common in intensive care units (ICUs), with an estimated prevalence ranging from 36 to 89%.^(1-3)^ Despite being a potential life-saving procedure, IMV is associated with complications, such as ventilator-associated pneumonia (VAP) and ventilator-associated tracheobronchitis (VAT).^(4,5)^ Although the incidence of these complications has decreased in recent decades due to improvements in preventive measures and care processes,^(6)^ it is estimated that the incidence of VAT is still 11% in patients receiving IMV.^(7)^ Patients with VAT have longer durations of mechanical ventilation, ICU stays, and hospital stays.^(7,8)^ Estimates suggest that approximately 12% of cases of VAT progress to VAP,^(7)^ suggesting that these two entities may be on a *continuum*.^(9)^ However, the relationship between VAT and increased mortality is unclear.^(7)^

Although there are many studies evaluating strategies for VAT prevention,^(10)^ there are limited data from clinical trials to determine whether VAT warrants antibiotic treatment, and only one ongoing clinical trial, which is still unpublished.^(11)^ Observational data have shown a possible benefit of antibiotic treatment in reducing VAT progression to VAP^(7,12)^ and a possible mortality benefit,^(13)^ but a meta-analysis showed no benefit of antibiotic treatment on clinical outcomes.^(10)^ Furthermore, the Infectious Diseases Society of America (IDSA) guidelines^(5)^ recommend against the routine treatment of VAT with antibiotics (weak recommendation, low quality of evidence). An online survey comprising 288 ICUs from 16 countries^(14)^ revealed considerable heterogeneity in the use of antibiotics for VAT treatment, with 42% of respondents reporting antibiotic use for all VAT patients, while 26% did not use it at all; the remainder used antimicrobials only under specific circumstances, such as in the presence of cardiovascular dysfunction. Hence, an apparent discrepancy is observed between clinical practice and current guidelines. These limitations of the current evidence are recognized by the heterogeneity in VAT treatment in clinical practice and reinforce the need for further studies in the field.^(5,6,15-17)^

The VATICAN (Ventilator-Associated Tracheobronchitis Initiative to Conduct Antibiotic Evaluation) trial is designed to address this gap by assessing whether a watchful waiting antibiotic treatment strategy is noninferior to routine antibiotic treatment for VAT regarding mechanical ventilation-free days (VFDs) among invasively ventilated patients with a clinical diagnosis of VAT. We hypothesize that the watchful waiting strategy will lead to less antimicrobial consumption with no impact on mortality or mechanical ventilation duration at the possible expense of an increased risk of VAP.

## METHODS

We used the recommendations for Interventional Trials (SPIRIT) guidelines for this report.^(18)^The final report will follow the Consolidated Standards of Reporting Trials (CONSORT) statement and its extension to noninferiority trials.^(19)^ The trial was registered with ClinicalTrials.gov (NCT05266066) before inclusion of the first patient.

### Design

The VATICAN is an investigator-initiated, multicenter, randomized, controlled, open-label, noninferiority clinical trial conducted to compare whether a watchful waiting antibiotic treatment strategy is noninferior to antibiotic treatment for seven days for VAT treatment.

The trial will be conducted in up to 50 Brazilian ICUs. The trial is partially nested in the IMPACTO MR platform,^(20)^ a research platform that collects prospective observational data from more than 50 ICUs in Brazil, with the VATICAN trial also allowing for the inclusion of ICUs outside the IMPACTO MR platform.

### Trial population

The target population of the VATICAN trial is patients with suspected VAT who do not have septic shock or clinical evidence of VAP. Patients who are mechanically ventilated for more than 48 hours at each participant site will be assessed daily by site investigators for eligibility. Mechanically ventilated patients will be screened during the first three weeks of mechanical ventilation, i.e., not on prolonged mechanical ventilation. We aim to include patients who met the following clinical criteria for VAT: (1) had at least one event of leukocytosis, leukopenia, left shift, fever, or hypothermia, and (2) met at least one criterion for worsening tracheal secretions. The main exclusion criteria were patients with hemodynamic instability due to probable infection, highly suspected VAP (either because of an evident new pulmonary infiltrate or persistently worsening gas exchange), who were currently on antimicrobial agents or who had another indication for antimicrobial treatment. These exclusion criteria ensure that no patients randomized in the trial will have a Clinical Pulmonary Infection Score (CPIS) ≥ 7, which was shown in a recent study to be very specific (0.89) and have a high positive predictive value (0.88) for VAP diagnosis.^(21)^Figure 1 presents the screening and eligibility evaluation for recruitment into the trial. The detailed inclusion and exclusion criteria are described in table 1.

**Figure 1 f01:**
[figure not shown]
Screening of trial participants and triage into the trial up to randomization. LRTI - lower respiratory tract infection; CT - computed tomography; LRT - lower respiratory tract; VAP - ventilator-associated pneumonia.

**Table 1 t1:** Inclusion and exclusion criteria of the VATICAN trial

**Inclusion criteria**
1. Adult patients (age ≥ 18 years old)
2. Admitted to ICU
3. Invasive mechanical ventilation for at least 48 hours
4. Presence of clinical criteria for VAP, defined as: a. Temperature > 38°C or < 36°C **OR** leucocyte > 12,000/mL or < 4,000/mL or > 10% immature forms **AND** b. New onset of purulent tracheal secretions **OR** change in secretion characteristics **OR** increase in secretions volume **OR** increased suctioning requirements
5. Lower respiratory tract microbiological sample under analysis or collection on the day of trial triage
6. Chest imaging (chest X-ray or computed tomography) on the day of trial triage
**Exclusion criteria**
1. Pregnancy or active lactation
2. Current use or indication of use of systemic antibiotics for any reasons
3. Hemodynamic instability, defined as new-onset hypotension unresponsive to fluid boluses or increase in vasopressor dose > 0.1mcg/kg/minute of norepinephrine or equivalent in the previous 6 hours
4. Worsening gas exchange, defined as an increase in the oxygen-inspired fraction ≥ 20% or an increase in PEEP ≥ 3cmH_2_O after a period of stability of ≥ 2 days
5. Prolonged mechanical ventilation, defined as an invasive mechanical ventilation duration ≥ 21 days
6. A new pulmonary opacity on chest image suggestive of new infectious infiltrates
7. Previous pulmonary disease that hampers the radiographic interpretation for VAP diagnosis
8. Previous diagnosis of VAP during hospitalization
9. Neutropenia (absolute neutrophil count < 1,000/mL)
10. Severe known immunosuppression
11. Tracheostomy on the day of trial triage
12. Prior inclusion in the trial in the last 30 days
13. Expected withholding or withdrawing of life support within 7 days
14. Patients unlikely to survive > 48 hours
15. Consent refusal to participate in the trial

ICU - intensive care unit; VAP - ventilator-associated pneumonia; PEEP - positive end-expiratory pressure.

### Randomization, allocation concealment, and blinding

Patients will be randomized in a 1:1 ratio to each treatment arm (Watchful Waiting Group *versus* Antibiotic Treatment Group for 7 days). Randomization lists will be generated by an independent statistician using R software^(22)^ in random block sizes to preserve allocation concealment and will be stratified by center and by suspected diagnosis of viral pneumonia. Randomization will be performed using a central online randomization system (RedCap) that is available 24 hours a day.

This is an open-label trial in which both patients and investigators are not blinded to the interventions, given the nature of the trial and the need to follow local treatment regimens based on local microbiology. The adjudicators and trial statisticians will be blinded to the treatment assignment.

### Trial treatments

Figure 2 presents the main elements of the trial protocol. In the Watchful Waiting Group, participants will not receive antimicrobials for VAT. Antimicrobials can be used, however, at the clinician’s discretion when other non-VAT-related indications ensue, such as progression to VAP, hemodynamic worsening or shock, newly confirmed or highly probable infection by the treating physician, unexplained new or worsened organ dysfunction or any other validated clinical indication for antimicrobial utilization. Antimicrobial initiation is not advised if lower respiratory tract cultures are positive and the patient does not develop other treatment indications.

**Figure 2 f02:**
[figure not shown]
Trial procedure description during the 7-day treatment protocol window. VAT - ventilator-associated tracheobronchitis; LRTI - lower respiratory tract infection VAP - ventilator-associated pneumonia; SOFA - Sequential Organ Failure Assessment; LRT - lower respiratory tract.

In the Antibiotic Treatment Group, participants received antimicrobials for seven days for the treatment of VAT. Five days of treatment is allowed for patients with complete clinical improvement, defined by the absence of fever, leukocytosis and improvement in tracheal secretions. Adjustments to the empirical antimicrobial treatment will be made after microbiological results are available, as appropriate. The antimicrobial choice will align with the recommended empirical antimicrobial choice for ICU-acquired lower respiratory tract infections based on the microbiota of each unit. We provide guideline-recommended antimicrobial choices in centers where an empirical regimen is not suggested. Antimicrobials for non-VAT-related indications will also be allowed in the antibiotic treatment group.

Each ICU enrolling patients in the trial is encouraged to follow the best practice guidelines and their institutional protocol for the care of critically ill patients,^(23)^ including a VAP prevention protocol. Nevertheless, the VATICAN trial will not directly influence best practices at each site. Inhaled antimicrobial agents will not be allowed during the trial. More information on the trial’s procedures is available in the Supplementary Material.

